### Good Clinical Practice Statement

This study will be conducted in accordance with the applicable Health Canada regulations, International Conference on Harmonisation (ICH) guidelines on current Good Clinical Practice (GCP), and the Declaration of Helsinki.

## List of terms and abbreviations

| Term/abbreviation | Definition                       |
|-------------------|----------------------------------|
| ART               | Antiretroviral therapy           |
| GCP               | Good clinical practice           |
| HIV               | Human immunodeficiency virus     |
| I-Score           | (ART) Interference-Score         |
| MUHC              | McGill University Health Centre  |
| PROM              | Patient-reported outcome measure |

## Summary

**Title:** Electronic capture through the Opal patient portal of a patient-reported measure of barriers to antiretroviral therapy adherence: a mixed method type 3 hybrid pilot study at a large Montreal HIV clinic

**Short title:** The I-Score/Opal Implementation Pilot Study

**Background:** Many people with HIV on antiretroviral therapy (ART) have trouble adhering to their treatment. Regular monitoring of barriers to ART adherence is clinically recommended, however, patient-provider communication around adherence is often inadequate. Our team thus decided to develop a new electronically administered patient-reported measure of barriers to ART adherence (the I-Score) to facilitate the systematic capture of this data for physician consideration in routine HIV care. To develop the tools and methods necessary for a controlled definitive trial to test the I-Score intervention, a pilot study was in order.

**Objectives:** The specific primary objectives of this pilot study are to evaluate perceptions of the I-Score intervention (Objective 1) and evaluate its implementation strategy (Objective 2). Its secondary objective (Objective 3) is to determine if the intervention shows promise and if the chosen outcomes are useful.

**Methods:** This 6-month study will adopt a one-arm mixed method type 3 implementation-effectiveness hybrid design and be conducted in a single clinical site, the Chronic Viral Illness Service of the McGill University Health Centre. It will be guided by tools of implementation science (e.g., frameworks, outcomes). Five HIV physicians and 30 of their HIV patients will participate. The intervention will involve having patients complete the I-Score with an adapted version of the Opal smartphone app, prior to meeting with their physician. Both the patient and the physician will have access to the I-Score results, for consideration during the clinic visits at Time 1 (T1), T2 (3 months), T3 (6 months). The implementation strategy will focus on patient and provider involvement, education, and training, as well as on promoting the intervention's adaptability. The strategy's cornerstone will be the hiring of an Application Manager to facilitate implementation. Implementation, patient, and service outcomes will be collected (T1, T2, T3). The primary outcome of this pilot study is the intervention's acceptability (target: mean scale score of 4 on 5). Qualitative data obtained through provider focus groups (T2, T3), patient interviews (T2, T3) and the Application Manager's field notes (T1-3) will serve especially to evaluate the implementation strategy and inform any methodological adaptations.

### Timeline:

- January-February 2021: Physician and patient enrollment
- March 2021-August 2021: Data collection
- April 2021-October 2021: Data analysis
- September 2020-December 2021: Presentation and manuscript preparation (beginning with the protocol manuscript)

**Expected contributions:** This study will contribute data towards the planning of a definitive trial to test the efficacy of the I-Score intervention. Furthermore, it will generate rare data on electronic PROM interventions in routine HIV care that will help improve understanding of conditions for their successful implementation. It could also eventually lead to the implementation of a new tool for HIV care that could shift the HIV care paradigm toward a more patient-centered and preventative approach.

## Introduction

Routinely collecting data on patient-reported outcome measures (PROMs) for individual patient care may benefit both people living with HIV and their providers, yet it is seldom done in HIV clinical practice (Kall et al., 2020). For patients, it may help ensure that HIV care is person-centered and in line with their needs (Kall et al., 2020). For providers, given the multidimensional and chronic nature of HIV clinical assessment and follow-up, the use of PROMs could facilitate efficient application of clinical guidelines in a context of time and resource constraints (Kjær et al., 2018).

The management of antiretroviral therapy (ART) adherence for the treatment of HIV provides a case in point. Successful ART remains essential to a near-normal life expectancy; however, many on ART have suboptimal adherence (Bezabhe et al., 2016; Ortego et al., 2011), even on single-tablet regimens (Cohen et al., 2020). In a recent study, only 23% percent of adults initiating a single-tablet regimen were considered adherent over a six-month period versus 12% among those who initiated a multiple tablet regimen, based on prescription fill dates (Cohen et al., 2020). Clinically recommended strategies to foster adherence include ongoing monitoring of barriers to adherence among people living with HIV (DHHS, 2019). Yet, several studies point to inadequate patient-provider communication around ART adherence and its impediments (e.g., Barford et al., 2006; Beach et al., 2015; Malta et al., 2005; Laws et al., 2013; Wilson et al., 2010) and many HIV providers underestimate their patients' adherence difficulties (Fredericksen et al., 2012; Miller et al., 2002). In addition, individuals with HIV collectively report a multitude of barriers to adherence, including a variety of cognitive, emotional, social and material issues as well as health service-related barriers (Engler et al., 2018; Shubber et al., 2016), the proper evaluation of which may be time-consuming for providers (Genberg et al., 2015).

For these reasons, with patient (Lessard et al., 2019) and provider (Toupin et al., 2018) involvement, we are developing a PROM of barriers to ART adherence, the Interference-Score (or I-Score), for electronic administration. I-Score data will be collected from patients and fed back to their providers via Opal, a patient portal and smartphone app. This award-winning app (Kildea et al., 2019), which is currently in use at the Cedars Cancer Centre of the McGill University Health Centre (MUHC), will be configured to respond to the needs of patients with HIV. Opal gives patients access to their appointment schedules, laboratory test results, educational material, waiting room management tools, and PROMs. Electronic administration of our PROM was crucial as it simplifies score integration within the clinical workflow, allows for longitudinal presentation of scores as well as remote monitoring, and through Opal, it provides access to several useful and potentially empowering patient-centered functions.

## Aim and objectives

With the present mixed method pilot study, drawing on implementation science, the aim is to develop the methods and tools necessary to undertake a more robust evaluation of the implementation and effectiveness of the I-Score ePROM-within-Opal innovation (henceforth, the I-Score intervention) in routine HIV care with individuals on ART. This study's primary objectives are to evaluate perceptions of the I-Score innovation (Objective 1) and evaluate the implementation strategy (Objective 2) in terms of recommended implementation science metrics for patient-reported outcome measure initiatives in routine care (Stover et al., 2020). Its secondary objective (Objective 3) is to determine if the intervention shows promise and the chosen outcomes are useful, by observing collected data on select effectiveness outcomes (patient and service outcomes).

## Guiding frameworks

It is important that a credible causal explanation of a digital health innovation's intended impacts be provided (Murray et al., 2016). Indeed, in an ePROM-based intervention, conceptual or theoretical frameworks specify the mechanisms through which the intervention is expected to have its effects (Greenhalgh et al., 2017), facilitating appropriate outcome selection and the interpretation of results (Greenhalgh et al., 2005).

This pilot study will be guided, in part, by an intervention logic chain, depicted by the boxes in Figure 1, adapted from the frameworks of Greenhalgh and colleagues (2005; 2017). The core of the intervention is encompassed by the dashed line. The left arrow presents the key components of the implementation framework used, which will guide qualitative analysis. Specifically, these are the five broad domains of potential influence on implementation of Damschroder and colleagues' (2009) Consolidated Framework for Implementation Research (CFIR) within which are grouped 39 distinct constructs. Hence, it is assumed that flow through the logic chain will be affected by features of the intervention, settings, individuals, and implementation process involved. The CFIR is a flexible and widely used framework in implementation research, including for PROM-based initiatives (Stover et al., 2020). Asterisks indicate elements of the logic chain which will be examined as a part of this pilot study.

[figure not shown]

Figure 1. Guiding implementation framework and I-Score intervention logic chain.

Figure 2 is a framework, in progress, that presents the broad hypothesized relationships between the implementation strategy used for the I-Score and the categories of study outcomes addressed. Borrowing from the frameworks of Stover and colleagues (2020) and Santana and Feeny (2014), it, in part, conceives successful implementation of I-Score use in standard HIV care, as potentially generating cascading effects on service and patient outcomes. Asterisks indicate outcomes for which data will be collected as a part of this study.

[figure not shown]

Figure 2. Relationship between the I-Score implementation strategy and study outcomes.

## Methods

### Study design

This 6-month pilot study will adopt a one-arm mixed method type 3 implementation-effectiveness hybrid design and be conducted in a single clinical site (see Figure 3). Type 3 hybrid designs emphasize testing the implementation strategy of an evidence-based intervention, but merely observing data collected on intervention effectiveness (Curran et al., 2012). While syntheses of effectiveness evidence for PROM use in routine care have typically found mixed results, with inconsistent impacts on patient outcomes (e.g., Boyce et al., 2013, Valderas et al., 2008), a more recent systematic review finds the evidence supports PROM use in standard care, particularly to improve patient-provider communication and decision-making in clinical practice (Isaque et al., 2019). The hybrid design also seems justified, given international momentum for PROM use (Rutherford et al., 2020), which may build with the COVID-19 pandemic. Indeed, there are calls for a scale up of electronic PROMs implementation in this crisis for the remote follow-up of chronic conditions, in part, to better screen patients and promptly manage their needs (Marandino et al., 2020).

Mixed methods were adopted in this study as multiple methods are recommended for studying intervention implementation and its problems in complex systems, like HIV clinics (Peters et al., 2013). Regarding the integration of the quantitative and qualitative data collected, this will occur toward study end within a convergent parallel design (Creswell and Plano Clark, 2011). Those directly involved in the analyses will decide upon the specifications of integration. Reporting of this study will seek to satisfy the standards of Good Reporting of a

Mixed Methods Study (O’Cathain et al., 2008) and the Standards for Reporting Implementation Studies (Pinnock et al. 2017).

### Setting and participants

The study setting is a large hospital-based clinic in Montreal, Quebec, Canada. This clinic, the Chronic Viral Illness Service (CVIS) of the MUHC, offers multidisciplinary care to approximately 2000 adults living with HIV. Five physicians treating individuals with HIV at the CVIS will be recruited to participate as well as 30 of their adult patients. This sample size amply meets rule of thumb recommendations for one-arm pilot studies (Sim & Lewis, 2011). Patients must be confirmed HIV-positive, have a history of known or suspected adherence problems in the past year, be aged at least 18 years old, be on or beginning combination ART, be literate in English or French, and own a smartphone. Full details on eligibility are presented in the next section. Ten female patients will be recruited, to ensure sufficient representation of women living with HIV (Public Health Agency of Canada, 2018).

[figure not shown]

Figure 3. Pilot study design.

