#### Inclusion criteria

- be aged 18 years or older
- be diagnosed with HIV-1 infection
- be treated with a combination antiretroviral therapy (composed of 2 to 3 different drugs)
- have had known or suspected adherence problems in the past 12 months based on a detectable viral load test result per local standards, patient report, and/or report by the healthcare team (by the physician, nurse, social worker or pharmacist)
- be treated for HIV at the Chronic Viral Illness Service of the McGill University Health Centre
- be able to speak and understand either French or English
- possess a smartphone with an appropriate data plan and/or home Wi-Fi connection

- be willing to download the smartphone app

Patients many not participate if they...

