### **Objective 3 -Determine preliminary intervention and effectiveness outcome utility**

This pilot study will collect data on one service outcome, patient management. It will be verified with a checklist submitted to participating physicians to allow them to record, per patient encounter, if they received the I-Score results on time, if they reviewed them prior to or during the clinic visit, if they were discussed during the visit, and if the I-Score identified concerning barriers. Then, they will check off any clinical actions that were taken based on the I-Score results or any related patient-provider discussion (e.g., recording issues in medical notes, referring to another health professional, ordering a test, changing a medication or treatment, providing advice or education). See the Appendix for the physician checklist.

The patient outcomes assessed in this pilot are barriers to adherence, adherence and viral load. Barriers to ART adherence will be assessed at T1, T2, and T3, with our previously described ePROM. Adherence will be examined with the Self-Rating Scale Item (SRSI) (Feldman et al., 2013) at T1, T2, and T3. It is a one item measure of treatment adherence (i.e. “Rate your ability to take all your medications as prescribed” [over the past 4 weeks], rated on a 6-point scale (i.e. Very poor, Poor, Fair, Good, Very good, and Excellent). Viral load, a clinical indicator of viral activity (e.g., infectiousness) and treatment response, will be treated as a dichotomous variable based on whether, as indicated in the patient’s medical file, the HIV RNA viral load is detectable (over 50 copies), or not. Undetectability is a goal of HIV treatment. The most recent viral load test result at T1 and T3, will be collected.

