Regarding the patient outcomes of Objective 3, barriers to adherence and adherence will be summarized with the minimum, the maximum, the mean, and the standard deviation. Viral load will be reported by absolute and relative frequencies, as it is considered a dichotomous variable. For the service outcome obtained from the physician checklist, we will report the proportion of clinic visits when physicians took action based on the I-Score results, among the visits where an adherence barrier of concern was identified by physicians. Proportions will be reported for T1, T2 and T3 and globally, across time periods. To evaluate evidence of a statistically significant difference in our chosen effectiveness outcomes, we will run a Student's paired t-test for barriers to adherence and adherence and a McNemar test for viral load, between T1 and T3. To complete the analysis of the service outcome, we will use a logistic regression model, considering only the visits where an adherence barrier of concern was identified by physicians. The dependent variable is the binary variable of whether or not an action was taken by physicians and the independent variable is the time, considered as a factor with three independent levels (T1, T2 and T3). We will test the null hypothesis that time has no effect on the probability of taking action, with a t-test on the regression coefficient. We will conclude the analysis by testing the null hypothesis of equality of proportions between all pairwise combinations of time points, with a Student's t-test between two proportions, performing a Bonferroni correction for multiple tests. For all analyses, a significance level of 5% will be adopted.

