### ***Adherence to your HIV medication***

10. Rate your ability to take all your HIV medications as prescribed, over the past 4 weeks.

- ☐ Very poor
- ☐ Poor
- ☐ Fair
- ☐ Good
- ☐ Very good
- ☐ Excellent

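### Eligibility sets no minimum time on ART and its two wordings differ, so the drug effect in any patient who starts treatment around T1 enters the T1-T3 viral load test

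*Protocol*

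**What the plan says.** - **Eligibility, narrative** (Protocol, Setting and participants): patients must "be on or beginning combination ART, be literate in English or French, and own a smartphone". The same paragraph adds "Full details on eligibility are presented in the next section".
- **Eligibility, formal list** (Inclusion criteria): patients must "be treated with a combination antiretroviral therapy (composed of 2 to 3 different drugs"). No duration or stability of treatment is required, and the exclusion criteria do not mention either.
- **Adherence criterion** (Inclusion criteria): patients must "have had known or suspected adherence problems in the past 12 months based on a detectable viral load test result per local standards". Patient report or healthcare-team report also qualifies.
- **Viral load outcome** (Objective 3): dichotomised at 50 copies. "The most recent viral load test result at T1 and T3, will be collected". No window is given and the result is not tied to the start of ART.
- **Self-report outcomes:** the adherence item in the T1 questionnaire reads "Rate your ability to take all your HIV medications as prescribed, over the past 4 weeks". The I-Score has the same 4-week recall (The I-Score intervention).
- **Analysis** (Quantitative analysis): a paired t-test for barriers and for adherence, and "a McNemar test for viral load, between T1 and T3", at the 5% level. Table 3 puts p at or below 0.05 in its threshold-for-success column for all three patient outcomes.
- **Data collected** (Quantitative component): the chart extraction names viral load only. The general health questions named are year of HIV diagnosis and treatment satisfaction.

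**The concern.** There is no control group to absorb the effect of starting ART. For a patient who begins at or shortly before T1, the T1 viral load may predate treatment or fall very early in it. The T3 value comes after about six months of drug. A move from detectable to undetectable is then what ART is meant to do, whether or not the I-Score contributes. The McNemar test counts that pair as improvement.

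A narrower problem affects the two self-report outcomes. A patient who had no ART prescription for part of the 4 weeks before T1 is asked to rate medication-taking, and barriers to it, over a window that includes untreated time. The adherence item offers no not-applicable answer.

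Objective 3 is where the protocol asks whether the intervention shows promise, and the pilot is meant to inform a definitive trial. Drug effect could be read there as promise. If the ART start date is never collected, no later analysis can separate these patients.

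**Working it through.** **Plan's own figure.** The sample of 30 rests on a cited rule of thumb: "This sample size amply meets rule of thumb recommendations for one-arm pilot studies". No effect size, power or discordance rate is given, so there is no calculation to reproduce.

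**Step 1: the two wordings.** The narrative admits patients on ART or beginning it; the list admits patients being treated with it. The second is narrower in tone, but someone treated for one day meets both. Treating the list as definitive therefore does not remove the issue.

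**Step 2: McNemar, idealised case.** Let k patients go from detectable to undetectable, none go the other way, and all others stay unchanged. Then:
- uncorrected chi-square = (k − 0)²/k = k, on 1 df
- continuity-corrected chi-square = (k − 1)²/k, on 1 df
- exact two-sided p = 2 × 0.5^k

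| k of 30 | Uncorrected | Corrected | Exact |
|---|---|---|---|
| 3 (10%) | 3.00, p = 0.083 | 1.33, p = 0.248 | 0.250 |
| 4 (13%) | 4.00, p = 0.046 | 2.25, p = 0.134 | 0.125 |
| 5 (17%) | 5.00, p = 0.025 | 3.20, p = 0.074 | 0.063 |
| 6 (20%) | 6.00, p = 0.014 | 4.17, p = 0.041 | 0.031 |

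The protocol does not say which version applies. The result depends on that choice at 4 and 5 pairs, but not at 6.

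**Step 3: with background change.** Simulation with n = 30, two-sided 5% and no I-Score effect. Assumptions, none of them from the documents: 80-90% of starters suppressed at T3, and 3-10% of the other patients discordant in each direction. The share of trials with p at or below 0.05 was:

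| Starters | Uncorrected | Exact |
|---|---|---|
| 0 | 1-5% | 0-1.4% |
| 3 | 10-21% | 1-6% |
| 6 | 29-60% | 19-39% |
| 8 | 49-85% | 38-73% |

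At the protocol's 80% retention benchmark (0.80 × 30 = 24 completers), 6 starters give 34-66% uncorrected and 22-42% exact.

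**Step 4: paired t-test.** The documents give neither the size nor the direction of any shift in starters. For illustration only: 6 of 30 patients shifted by 1 or 2 SD of the change score give rejection in 14% or 34% of trials, against a nominal 5%. With 3 patients the figures are 7% and 12%.

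**The case against.** **Few patients may be involved.** The narrative defers to the formal list, and that list also requires an adherence problem in the past 12 months. A patient who has never taken ART would seldom meet it. This stands: the number of true starters is probably small, and with 3 of them the inflation is modest.

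**A reader might infer that the typical participant is a lapsed patient with a detectable viral load who restarts at T1.** The documents do not support this. They do not mention restarting, and patients can qualify on their own report or the care team's, with no detectable result and no interruption.

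**A reader might infer that every starter or restarter has an invalid T1 self-report.** That goes too far. A patient who lapsed while holding a prescription can validly rate how well it was taken and what got in the way; a poor rating is the construct itself. The defect is confined to patients with no prescription for part of the recall window.

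**Renewed adherence is part of the target effect.** This stands as well. Excluding everyone who lapsed would remove patients the study is meant to recruit.

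**Effectiveness data are secondary and described as only observed.** Quantitative analysis links the targets for proceeding to a definitive trial to Objectives 1 and 2. This limits the consequence but does not answer the point, because formal tests at 5% are planned and Table 3 labels their p-values as thresholds for success.

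**Analysis sets are commonly left to an SAP.** True, and their absence here is not the finding. Eligibility wording and the list of data to collect belong to the protocol.

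**Conclusion.** The point holds in limited form. The two eligibility statements differ, neither sets a minimum time on ART, and the start date is not collected. In a one-arm comparison, drug effect in recent starters therefore enters the viral load test. The adherence and I-Score comparisons are affected only for patients without a prescription for part of the 4 weeks before T1.

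The size depends on a number the protocol does not give. It would be tempting to say that four such patients are enough to produce a success result. That is so only with the uncorrected test, all four suppressed, and no change in anyone else; the exact and corrected tests need six. With background discordance, six starters give a false success in some trials (19-39% exact, 29-60% uncorrected, under the stated assumptions) but not in all.

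The primary outcome, acceptability, and the rest of Objectives 1 and 2 are untouched. It is a real bias in a secondary objective, and cheap to reduce.

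**What to change.** 1. Reconcile the treatment-status wording in Setting and participants with the Inclusion criteria. Which patients to admit is for the study team to decide.
2. At the T1 chart extraction, record the date of ART start and of any restart.
3. For Objective 3, base the T1-T3 comparisons of viral load, self-rated adherence and I-Score on patients already prescribed ART for a pre-set period at T1. For the two self-report measures this should be at least the 4-week recall window; the period for viral load should be fixed in advance.
4. Keep patients who lapsed while holding a standing prescription in the comparison.
5. List recent starters separately and descriptively, and show the all-patient result alongside.
6. State that regression to the mean remains. Some patients are selected on a detectable viral load and there is no control group, so the restriction removes only part of the bias.

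The cost is a sentence or two of text and one or two dates from a chart already opened for viral load. The downside is that a few patients leave the main Objective 3 comparison. Enrolment, the primary outcome and Objectives 1 and 2 do not change.
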